#### Substudy 1: Community Pool

The study design is a two-stage, cross-sectional, community-based study.

#### Study Population

Women aged 18-40 years will be recruited using a multistage sampling technique involving urban and rural areas. The polling booths will be selected randomly at the coordinating center by a random selection process. This study will be conducted in 6 zones of the country involving 10 centers that are likely to represent a majority of ethnic groups.

#### Inclusion Criteria

The following are the criteria for inclusion: women aged 18-40 years who are permanent residents of the area (>1 year), willing to participate in the study and sign informed consent, known to have PCOS, and not on treatment.

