#### Participant Selection

Women aged 18-40 years who are not pregnant or lactating and have been residing in the area for 1 year or more will be included in the study. Women who are known to have PCOS will be recorded for the purposes of PCOS prevalence and will only be evaluated in detail for substudy 2 if they are drug-naïve. Women taking oral contraceptives, steroids, antiepileptics, or other drugs known to interfere in glucose or lipid metabolism will not be evaluated in detail and will be excluded from the study.

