#### Sampling Design

A multistage cluster sampling technique is being used in this study. The first step in the sampling procedure will be to have representative data from the 6 zones (N, S, E, W, NE, and Central) of the country (Figure 1). The participating institutions from 6 zones were selected in view of location, logistics, feasibility, and the investigator profile. One urban and one rural Vidhan Sabha constituency near each institution will be selected. The choice of selection of districts and the constituencies will be given to the principal investigators at each site in order to make the study execution simpler. A rural district would mean 70% of subjects pursuing agriculture activities, while urban would mean that less than 30% have agriculture as the source of income.

After the constituencies are selected, the entire list of polling booths will be obtained from the Regional Election Commission offices. Polling booths from rural or urban constituencies will be selected to fulfill the required sample size using a random number table so that each polling booth has an equal chance to get selected. This procedure will be carried out at the coordinating center (SKIMS, Srinagar) by a third party not directly involved in the study. Next, the sites will procure the electoral roll, and voter IDs will be searched for women (aged 18-40 years) to be the potentially eligible subjects. The resulting list of women will be screened using a checklist for eligibility. If a woman is not eligible or refuses to participate in the study, the offer will go to the next woman in the list. If there is more than one eligible woman in a family, the sampling frame will also shift to the next in the voter ID list. The procedure will continue until a total of 1000 women (500 rural and 500 urban) are screened per center (Figure 2).

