**Figure 2 figure2:**
[figure not shown]
Flowchart for sampling design and workflow of the study. AE-PCOS: Androgen Excess and Polycystic Ovary Syndrome; AIIMS: All India Institute of Medical Sciences; GMC: Government Medical College; IPGMER: Institute of Post Graduate Medical Education & Research; MHRT: Maternal Health & Research Trust; NEIGRIHMS: North Eastern Indira Gandhi Regional Institute of Health and Medical Sciences; NIH: National Institutes of Health; NIRRH: National Institute for Research in Reproductive Health; OMC: Osmania Medical College; PCOS: polycystic ovary syndrome; PGIMER: Postgraduate Institute of Medical Education and Research; SKIMS: Sher-i-Kashmir Institute of Medical Sciences.

#### Estimation of Sample Size for Substudy 1

Sample size was calculated, primarily to estimate the prevalence of PCOS in the country. Previously reported prevalence rates of PCOS have varied from 3.7% to 22.3% [32,33]. For the purpose of calculation of sample size, we presume the prevalence of PCOS in India to be 10%. With an assumed prevalence of 10% and an absolute error margin of 1% in a 95% 2-sided confidence interval and making allowance for about 20% refusals or nonresponse, we need to target a total of 4500 women. Further, being a cluster design and taking a design effect of 2, a total of 9000 women aged 18-40 years will be studied from 10 centers (ie, 1000 per center, except for the 2 centers in Hyderabad, which have been designated with 500 each), half from a rural community and half from an urban community at each center.

Based on a pilot study previously conducted by the chief coordinator using a similar questionnaire [34], 30% (2700/9000) of the women are expected to screen positive (likely to have PCOS) on the screening questionnaire and therefore are required to be investigated in detail. Additionally, of the 70% (6300/9000) of women expected to screen negative on the screening questionnaire, 20% (1260/6300) will require examination and investigation in detail. This will make the sample size of women requiring detailed evaluation and blood testing a total of 3960 (N=2700+1260). Keeping in view the number of centers (N=10), each participant center will screen approximately 1000 women, and a total of 440 women who will be invited for detailed examinations: 20% (140/700) of screen-negative women and all 30% (300/1000) who screen positive (Figure 2).

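### The substudy 1 inclusion list makes known, untreated PCOS a condition of entry to the prevalence survey, contradicting the rest of the protocol; it is probably a drafting slip, but the likelier reading still drops treated known cases

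*Protocol article*

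**What the plan says.** Under the heading for the substudy 1 community pool, the Inclusion Criteria section gives a single list joined by 'and'. A woman must be aged 18-40, a permanent resident for more than a year, and "willing to participate in the study and sign informed consent, known to have PCOS, and not on treatment". No 'or', 'if' or 'including' makes the PCOS item optional.

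Other sections of the protocol article describe a different population:

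- **Participant Selection** (substudies 1 and 2): "Women aged 18-40 years who are not pregnant or lactating and have been residing in the area for 1 year or more will be included". On known cases: "Women who are known to have PCOS will be recorded for the purposes of PCOS prevalence". Being drug-naive is required only for their detailed evaluation in substudy 2. The section's last sentence, however, excludes women on oral contraceptives, steroids, antiepileptics and drugs affecting glucose or lipid metabolism from the study.
- **Exclusion Criteria**: repeats the drug exclusions, adding androgens, for substudy 1.
- **Sampling Design**: from the electoral roll, "voter IDs will be searched for women (aged 18-40 years) to be the potentially eligible subjects". Then "The resulting list of women will be screened using a checklist for eligibility", and "If a woman is not eligible or refuses to participate in the study, the offer will go to the next woman in the list".
- **Estimation of Sample Size for Substudy 1**: assumes 10% prevalence and plans to examine 20% "of the 70% (6300/9000) of women expected to screen negative on the screening questionnaire".
- **Study Tool: The Questionnaire** and **Field Activities**: the questionnaire is there to find probable PCOS, and a sample of screen-negative women is also examined.

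**The concern.** A prevalence survey has to admit women without regard to whether they have the disease. Here the only formal inclusion list for substudy 1 names disease status, and treatment status with it, as conditions of entry. The list matters in practice because Sampling Design applies an eligibility checklist before screening and replaces each ineligible woman with the next on the roll until the quota is full. A center that filled its quota would see nothing unusual in its totals, whichever women had been passed over.

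The primary estimate of substudy 1 is at stake, and so is the source of the screen-negative comparison group. The damage depends on how the phrase is read, and the eligibility sections do not settle that.

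**Working it through.** **1. The plan's own figures, and what they presuppose.** Inputs from Estimation of Sample Size for Substudy 1: prevalence p = 0.10, absolute margin d = 0.01, 95% two-sided interval, 20% nonresponse, design effect 2.

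- n = z²p(1−p)/d². With z rounded to 2: 4 × 0.09 / 0.0001 = 3600.
- Nonresponse: 3600 / 0.8 = 4500. Design effect: 4500 × 2 = 9000. Both stated figures are reproduced exactly.
- With z = 1.96: 3458 / 0.8 = 4322.5, and × 2 = 8645. The stated target is about 4% above this, on the safe side.
- Centers: 8 × 1000 + 2 × 500 = 9000.
- Detailed evaluations: 0.30 × 9000 = 2700, plus 0.20 × 6300 = 1260, total 3960.

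The arithmetic is sound, and it presupposes a sample of mostly undiagnosed women.

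**2. Literal reading of the inclusion list.** Every woman enrolled is a known case, so the sample proportion is 1 by construction and p(1−p) = 0. The 10% prevalence, the 6300 screen-negatives and the 1260 examined negatives could not arise as planned. Even if every woman with PCOS at the assumed 10% were diagnosed and untreated, filling 9000 places would mean going through at least 9000 / 0.10 = 90,000 women. The inclusion list and the sample-size section cannot both hold.

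**3. Likelier reading: known cases may enter if untreated.** Set three sections side by side.

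| Section | Treated known case |
|---|---|
| Participant Selection, on known PCOS | Recorded for prevalence; only detailed evaluation needs drug-naive status |
| Participant Selection, last sentence, and Exclusion Criteria | Excluded from the study if on a listed drug |
| Inclusion Criteria | Not eligible, because on treatment |

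Let π be the true prevalence and t the share of all cases that are known, treated and passed over. If only cases are removed, the expected sample proportion is

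π(1−t) / (1−πt),

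which is below π for any t > 0. The drug exclusions also remove some women without PCOS. If u is the share of non-cases removed, the proportion becomes

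π(1−t) / [π(1−t) + (1−π)(1−u)],

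which is below π whenever t > u. That is the expected direction if women with PCOS take the listed drugs, or are treated, more often than other women.

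**4. Size.** The documents give neither t nor u, so the bias cannot be computed. A threshold can be set from the plan's own figures, taking u = 0: a one-point fall from 10% to 9% needs 0.10(1−t) / (1−0.10t) = 0.09, so 0.091t = 0.01 and t = 0.11. Losing about 11% of cases this way would shift the estimate by the whole planned margin. This is a yardstick, not an estimate of t.

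**The case against.** The strongest reply is that nobody could run the survey on the literal wording. Participant Selection, Study Population, Sampling Design, the sample-size section, the questionnaire section and Field Activities all point the other way, and a center expecting 70% screen-negatives would notice at once. The eligibility questionnaire has 7 questions, is not reproduced, and was pilot-tested and modified over several investigator meetings. It may never have carried the phrase. All of this stands: the phrase is almost certainly a wording error, and it is not evidence that the survey enrolled, or will enroll, only diagnosed women.

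A reader might also infer that known cases would be favored when women are replaced, so that prevalence would be overstated. The documents do not support that. Sampling Design passes the offer to the next woman on the list, and nothing permits choice by disease status. The literal condition is all-or-none and cannot produce a small enriched fraction.

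What the reply does not remove is the conflict over treated known cases. The charitable reading resolves the absurdity, but leaves Inclusion Criteria and Exclusion Criteria against the sentence in Participant Selection that records known cases for prevalence. Participant Selection is itself divided on the matter, because its last sentence excludes women on listed drugs from the study.

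**Conclusion.** The point holds as an internal contradiction in the eligibility rules of substudy 1. As written, the inclusion list would leave no prevalence to estimate. That reading is ruled out by the rest of the protocol and should be treated as a probable slip. On the likelier reading, treated known cases are lost to a survey that elsewhere undertakes to count them, and the estimate is biased downward. The size is unknown. The direction rests on the exclusions removing a larger share of cases than of non-cases. Whether the fault reached the field depends on the eligibility questionnaire, which is not shown. The sample size is unaffected.

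**What to change.** 1. In Inclusion Criteria for substudy 1, remove PCOS status and PCOS treatment as entry conditions. State that all sampled resident women aged 18-40 enter the prevalence denominator regardless of PCOS status, subject to the exclusions unrelated to PCOS or drugs that the protocol already lists, such as pregnancy and lactation.
2. Record known cases, treated or not, for prevalence, as Participant Selection says.
3. Apply the drug-naive and drug-exclusion conditions only to detailed evaluation and substudy 2, and reconcile Participant Selection (including its last sentence), Inclusion Criteria and Exclusion Criteria to match. Deleting the phrase alone would leave the drug exclusions still dropping treated cases.
4. Confirm that the 7-question eligibility questionnaire does not carry the phrase. The Results section says community recruitment began in 2018, so also establish which rule the centers applied and report it with the prevalence estimate.

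The cost is a few sentences in the eligibility sections and a check of one form. The target stays at 9000. Women on listed drugs would be counted without detailed evaluation, so the plan should say how their PCOS status is assigned.

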#### Exclusion Criteria

Pregnant or lactating women and those with cognitive limitations, physical limitations, or both that prevented them from answering the questionnaire will be excluded from the study.

Women with a history of drug intake such as steroids, androgens, oral contraceptives, antiepileptics, or drugs known to interfere in glucose or lipid metabolism will also be excluded.

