## Plain English Summary

Polycystic ovary syndrome (PCOS) is a multifactorial disorder with unknown etiology and numerous clinical manifestations in reproductive-aged women around the world. The metabolic abnormalities linked to this syndrome include type 2 diabetes, insulin resistance (IR) obesity, abnormal glucose tolerance (AGT), and cardiovascular diseases (CVD). The sketchy data and escalating prevalence of PCOS and associated comorbidities among Indian women led to organization of a multidisciplinary brainstorming meeting held September 11, 2014, at Indian Council of Medical Research (ICMR) headquarters, and the ensuing recommendations suggested formulation of the ICMR–PCOS Task Force to conduct a multicentric, multiphase study among Indian women with PCOS.

This is a multicentric, multispecialty study with a common comprehensive predesigned protocol involving 10 centers located in the 6 zones of the country. The women from the community (rural and urban) will be screened using a validated screening questionnaire, after obtaining a written informed consent from the subjects. The proforma will capture all details about menstrual cyclicity, acne, hirsutism, socioeconomic status, family history of PCOS, etc. The national prevalence will be calculated from the community pool for substudy 1. All biochemical and hormonal analysis will be done by standard assays using similar kits, reagents, and equipment. Ultrasonography (US) including magnetic resonance imaging (MRI) of the abdomen will be performed using a common approved protocol. The various comorbidities such as AGT, nonalcoholic steatohepatitis, and sleep apnea will be evaluated from both the pools (ie, hospital cohort and community cohort in substudy 2). The interventional randomized double-blind trial (ie, oral contraceptive pills [OCPs] vs metformin) will be conducted at only 2 centers for substudy 3. Apart from this, a knowledge, attitude, and practices survey of service providers in the public health system will be conducted to understand the training needs and gaps in the health system addressing PCOS management.

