The 1990 National Institutes of Health (NIH) consensus conference criteria will be taken as the qualifying criteria. This necessitates the presence of the following 2 criteria: (1) oligoovulation or anovulation (intermenstrual interval ≥35 days, presence of ≤8 cycles per year, or both) and (2) clinical signs, biochemical evidence, or both of hyperandrogenism after ruling out disorders with similar clinical presentation such as hyperprolactinemia, Cushing syndrome, congenital adrenal hyperplasia, and androgen-secreting tumors with specific laboratory analysis (cortisol, 17OHP, and DHEAS). To compare, the 2003 Rotterdam criteria and the 2009 Androgen Excess and PCOS (AE-PCOS) Society criteria will also be employed. Therefore, US examination to satisfy the diagnosis of PCOS by these criteria will be done. A common standard operating procedure for abdominal examination (liver, pancreas, ovary, and uterus) will be adhered to with a built-in system to minimize interobserver and equipment variations. The 2003 Rotterdam criteria necessitate the presence of 2 of the following 3 criteria: (1) oligoovulation, anovulation, or both; (2) clinical signs, biochemical evidence, or both of hyperandrogenism; and (3) polycystic ovary in US. The 2009 AE-PCOS Society criteria necessitate the presence of the following criteria: (1) oligoovulation and/or anovulation (intermenstrual interval ≥35 days, presence of ≤8 cycles per year, or both) and/or polycystic ovary in US and (2) clinical signs, biochemical evidence, or both of hyperandrogenism. To exclude etiologies that could mimic PCOS like Cushing syndrome, late-onset adrenal hyperplasia, or androgen-producing neoplasm, we will exclude thyroid disorders, renal hyperplasia, hyperprolactinemia, and late-onset congenital adrenal hyperplasia by medical history and hormone tests. This will further serve to unravel various comorbidities such as AGT, metabolic syndrome, IR, cardiovascular risk, psychiatric morbidities, and impairment of QOL (Figure 3). Besides, these women will be evaluated for risk factors such as birth weight, parental history of gestational diabetes or PCOS, risk of low birth weight, precocious pubarche, prepubertal obesity, antiepileptic drug intake, familial association with lifestyle diseases, etc. Abdominal MRI for comparing ovarian morphology will also be done at a selected center (SKIMS, Srinagar) using the predesigned uniform protocol.

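### The protocol gives conflicting rules on whether women with known, treated PCOS count toward prevalence; under the written exclusion and replacement rules they drop out of the survey

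*Protocol article*

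**What the plan says.** Four sections of the Protocol article bear on who is counted.

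- **Participant Selection** (covering Substudies 1 and 2): "Women who are known to have PCOS will be recorded for the purposes of PCOS prevalence", with drug-naïve status required only for detailed evaluation in Substudy 2. The last sentence of the same section says that women *taking* oral contraceptives, steroids, antiepileptics or drugs affecting glucose or lipid metabolism "will not be evaluated in detail and will be excluded from the study". It makes no exception for known PCOS.
- **Inclusion Criteria** (Substudy 1): the list ends with "known to have PCOS, and not on treatment".
- **Exclusion Criteria** (Substudy 1): the excluded group is "Women with a history of drug intake such as steroids, androgens, oral contraceptives, antiepileptics, or drugs known to interfere in glucose or lipid metabolism". The word here is *history*, which is wider than *taking*.
- **Sampling Design**: "If a woman is not eligible or refuses to participate in the study, the offer will go to the next woman in the list". Also: "The procedure will continue until a total of 1000 women (500 rural and 500 urban) are screened per center".

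The Plain English Summary describes the Substudy 3 comparison as "oral contraceptive pills [OCPs] vs metformin", and Randomization (Drug Intervention) names the same two drugs. Evaluation Methods lists, among the risk factors to be assessed, "antiepileptic drug intake, familial association with lifestyle diseases".

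**The concern.** National prevalence is the first primary objective. A field team cannot tell from these sections whether a woman with diagnosed PCOS who is on treatment is a case, a non-participant, or someone to be replaced. If the team follows the Inclusion Criteria, Exclusion Criteria and Sampling Design, she is replaced before anything is counted.

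That selection is related to the outcome. Oral contraceptives are named in the exclusion, metformin acts on glucose metabolism, and both are treatments for PCOS in this protocol. Being drug-naïve is a reasonable condition for interpreting hormone and metabolic tests. It is not a reasonable condition for belonging to the population whose prevalence is being estimated. The error would be systematic, so a larger sample would not reduce it.

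A second conflict has the same source. Antiepileptic intake cannot be assessed as a risk factor among women who are ineligible because of it.

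**Working it through.** **Inputs from the protocol** (Estimation of Sample Size for Substudy 1): prevalence p = 10%, margin 1 percentage point, two-sided 95% interval, 20% nonresponse, design effect 2; 4500 women before the design effect and 9000 after.

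**The plan's own figure.** n = z²p(1−p)/d². With z = 2: 4 × 0.10 × 0.90 / 0.01² = 3600; 3600/0.8 = 4500; × 2 = 9000. Both stated figures reproduce exactly (z = 1.96 would give about 4322 and 8643). The sample size is not in dispute; the 1-point margin serves as the yardstick below.

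**Assumed inputs.** Let t be the share of women with PCOS removed by the drug rule and u the share of women without PCOS removed. The protocol gives neither, so both are varied.

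**Reading 1: everyone on these drugs is excluded and replaced.**

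Observed prevalence = p(1−t) / [p(1−t) + (1−p)(1−u)].

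Example, t = 20%, u = 5%: 0.08 / (0.08 + 0.855) = 8.56%.

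| | t = 10% | t = 20% | t = 30% |
|---|---|---|---|
| u = 0 | 9.09% | 8.16% | 7.22% |
| u = 5% | 9.52% | 8.56% | 7.57% |

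Setting the expression equal to 9% gives the t at which the shortfall reaches the 1-point margin: t = 1 − 0.09(1−p)(1−u)/(0.91p) = 1 − 0.8901(1−u).

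- u = 0: t ≈ 11%
- u = 2%: t ≈ 13%
- u = 5%: t ≈ 15%
- u = 10%: t ≈ 20%

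At t = u the factors cancel and the bias is zero. At t < u it is upward: t = 10%, u = 20% gives 0.09/(0.09 + 0.72) = 11.1%.

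**Reading 2: known PCOS is counted, but drug users without PCOS stay excluded.** If every removed case is a known case and is restored, observed prevalence = p / [p + (1−p)(1−u)]. At u = 5%: 0.10/(0.10 + 0.855) = 10.47%, an overstatement. It is correct only at u = 0.

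**Reading 3: drug users with and without PCOS stay in the survey, and the cases among them are counted.** The result is 10% for any t and u. None of the sections sets out this rule in full.

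**Antiepileptics.** Under *history* (Exclusion Criteria), no woman ever exposed is eligible and the factor cannot be studied. Under *taking* (Participant Selection), past users remain and current users do not.

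**The case against.** The strongest reply is that the Participant Selection sentence is the specific rule and already counts treated known cases, so nothing is lost from the numerator. That reading is available, and it is why the point is a conflict of rules and not an established loss of cases. It does not settle the matter: the same section ends by excluding current users from the study without exception, and counting treated cases while other drug users stay excluded overstates prevalence.

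It can also be said that the Inclusion Criteria are a compressed list. Read literally, they would require every participant to have known PCOS, which is impossible in a prevalence survey. That is fair, and little should rest on that item alone. The Exclusion Criteria and the replacement rule do not depend on it.

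Two further objections stand. Oral contraceptives are also used for reasons unrelated to PCOS, so u = 0 is a limiting case, and the direction of bias depends on t > u. And a self-reported, treated diagnosis does not by itself meet the NIH 1990 criteria, so such women cannot simply be added to the confirmed cases.

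A reader might also infer that urban–rural and regional comparisons are distorted because treatment is commoner where care is easier to reach. The protocol reports no treatment rates or access to care by area, so that inference is not supported.

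**Conclusion.** The conflict is in the text and affects the case count and the denominator of the primary prevalence estimate. Followed as written, the Substudy 1 criteria and the replacement rule remove women on oral contraceptives or metformin from both.

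A downward bias is plausible, because the excluded drugs include PCOS treatments, but it is conditional on t > u and its size cannot be fixed from the protocol. Over the assumed range (t of 10% to 30%, u of 0 to 5%), a true 10% would appear as about 7.2% to 9.5%. The shortfall passes the planned 1-point margin at t of about 11%, 15% or 20% for u of 0, 5% or 10%. The documents do not support an unconditional statement that national prevalence will be underestimated.

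The antiepileptic inconsistency holds whatever the size of the prevalence bias: completely under *history*, for current users only under *taking*.

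**What to change.** 1. Reconcile Participant Selection, Inclusion Criteria and Exclusion Criteria, including *taking* versus *history*, so that drug use restricts hormonal and metabolic testing only and does not decide membership of the prevalence survey.
2. Keep drug users in the denominator. Report known treated PCOS as its own case category, and give prevalence with and without it.
3. For drug users whose status cannot be confirmed under the NIH 1990 criteria, give bounds: for example, a lower figure counting none as cases, and a further figure applying the rate seen in non-users to those without a diagnosis.
4. Report exclusions by reason.
5. For centres already fielded (recruitment began in 2018), use eligibility records for a sensitivity analysis only where they were kept. The protocol does not show that PCOS status was recorded or retained for ineligible women; the logbook it mentions is described under Substudy 3.
6. Either keep antiepileptic users in the survey or drop antiepileptic intake from the risk factors in Evaluation Methods.

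The cost is revised wording, some classification from history instead of testing, and one extra sensitivity analysis.
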